### Statistical methods

IBT and WLC groups will be compared on baseline characteristics using analyses of variance for continuous and chi-square tests for categorical variables. If characteristics differ significantly and are predictive of outcome, they will be considered as covariates in subsequent analyses. The primary outcome

will be the percent of participants in IBT and WLC conditions with biochemically-confirmed illicit opioid abstinence at the 24-week assessment, evaluated based on a Cochran-Mantel-Haenszel (C-M-H) chi square test with site as the stratification variable. Primary analyses will include all randomized subjects independent of early dropout and with missing urine specimens considered positive for illicit opioids, consistent with an intent-to-treat approach (Armitage, 1983). The Breslow-Day test will be used to test homogeneity of the treatment effects across sites. If applicable, logistic regression will be used to adjust for baseline covariates confounded with treatment group. Though not the primary outcome, abstinence at other monthly assessments will be compared across treatments with Bonferroni-adjusted C-M-H tests to control experiment-wise type I error rate below  $\alpha=.05$ . Within the IBT group, generalized estimating equation (SAS, PROC GENMOD) will be used to characterize the temporal trend in abstinence across assessments. Fixed factors will include recruitment site and the within-subject factor, assessment time, along with their interactions. Repeated measures analyses of variance (SAS, PROC MIXED) will be used to compare groups on continuous outcomes (e.g., past-month frequency of illicit opioid and IV use, ASI subscales, BDI, HIV knowledge, OD risk knowledge). If significant treatment by time interactions are detected, partial F-tests will be used to examine simple effects of treatment at each assessment. Additional repeated measures analyses will characterize temporal patterns in IBT-specific outcomes (e.g., BUP adherence, IVR utilization, satisfaction). For WLC participants who after 24 weeks transition to IBT, estimates of abstinence will be obtained with corresponding 95% confidence intervals at each assessment. Statistical analyses will be performed using SAS V9.4 (SAS Institute, Cary, NC).

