**Statistical methods.** IBT and WLC groups will be compared on baseline characteristics using analyses of variance for continuous and chi-square tests for categorical variables. If characteristics differ significantly and are predictive of outcome, they will be considered as covariates in subsequent analyses. The primary outcome will be the percent of participants in IBT and WLC conditions with biochemically-confirmed illicit opioid abstinence at the 24-week assessment, evaluated based on a chi square test. Primary analyses will include all randomized subjects independent of early dropout and with missing urine specimens considered positive for illicit opioids, consistent with an intent-to-treat approach (Armitage, 1983). We hypothesize that participants receiving IBT will achieve significantly greater biochemically-verified illicit opioid abstinence relative to WLC. If applicable, logistic regression will be used to adjust for baseline covariates confounded with treatment group. Though not the primary outcome, abstinence at the other monthly assessments will be compared between groups with Bonferroni-adjusted chi square tests to control experiment-wise type I error rate below  $\alpha=.05$ . Within the IBT group, generalized estimating equation (SAS, PROC GENMOD) will be used to characterize the temporal trend in abstinence across monthly assessments. Additional outcomes will include IV opioid use, other (non-opioid) drug use, retention, BUP adherence, IVR utilization, and patient satisfaction. Repeated measures analyses of variance (SAS, PROC MIXED) will be used to compare groups on continuous outcomes (e.g., past-month frequency of illicit opioid and IV use, ASI subscales, BDI, HIV+HCV knowledge). If significant treatment by time interactions are detected, partial F-tests will be used to examine simple effects of treatment at each assessment. Additional repeated measures analyses will characterize temporal patterns in IBT-specific outcomes (e.g., BUP adherence, IVR utilization, satisfaction). Statistical analyses will be performed using SAS statistical software Version 9.4.

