**Participants randomized to receive IBT provided significantly more illicit opioid-negative urine specimens than those randomized to WLC at Weeks 4 (88% vs. 0%), 8 (84% vs. 0%), and 12 (68% vs. 0%) assessments ( $p$ 's<.001).** They also demonstrated greater reductions in past-month frequency of IV use ( $p$ <0.001). We also saw evidence of unexpected IBT-related benefits beyond abstinence, particularly in the area of psychological distress. IBT participants demonstrated greater reductions on the Beck Depression Inventory (BDI), with IBT participants reporting lower levels of depression at Weeks 4, 8, and 12 ( $p$ 's $\leq$ .01)(Fig 4; dotted line denotes a score suggesting need for treatment; Sprinkle et al., 2002). A similar pattern was seen on the Addiction Severity Index (ASI) Psychiatric subscale ( $p$ =.02). These data suggest that IBT may produce improvements in psychological symptom severity among waitlisted opioid-dependent individuals, even without formal counseling.

Study retention was high among IBT and control participants (92% and 80%, respectively) and did not differ between groups ( $p$ =.42). IBT participants' adherence with the treatment components was also excellent. For example, participants took 99% of scheduled doses and completed 96% of daily calls, which averaged 1.24 $\pm$ 0.4 minutes. They satisfied 96% of random call-backs, with 85% of specimens collected at those random visits negative for illicit opioids. The HIV+HCV application was associated with improvements in HIV- and HCV-related knowledge, and these improvements also persisted though 12-week follow-up. Finally, IBT participants' ratings of treatment satisfaction were high (4.6 $\pm$ 0.7 on a 5-point scale).

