### **Sample size justification**

The proposed sample size is based on having sufficient power for detecting treatment differences for primary and secondary outcomes. Regarding the percent of participants negative for illicit opioids at the 24-week assessment, power is estimated to be greater than 95% using  $\alpha=.05$  if true abstinence rates are as low as 60% vs. 15% for IBT and WLC groups, respectively. These estimates are more conservative than on our R34 outcomes, with lower abstinence predicted in IBT as we increase the duration to 24 weeks and move beyond a single research clinic for this Stage II trial. For secondary aims, effect sizes range from small to moderate. The estimated differences between conditions in mean change from baseline to 24 weeks corresponding to power=80% for representative ASI subscales are: Employment=.084 (ES=0.23), Psych=.076 (ES=0.36), Legal=.044 (ES=0.32), and Drug=.056 (ES=0.51). Similarly, power is 80% for detecting a mean difference of 4 units in the 24-week change in BDI (ES=0.30) which is smaller than we observed in our pilot trial. Lastly, power is estimated to be 80% to detect a mean absolute difference of 6% in the pre-post change in HIV knowledge scores (ES=0.39) and 5.5% (ES=0.34) for the pre-post change in OD knowledge scores. It should be noted that these ES's (Cohen d's) are expressed relative to the between-subject variability at baseline [i.e.  $(\Delta_{IBT}-\Delta_{WLC})/\sigma_{\text{between-subject}}$ ], not the variability in the change scores [i.e.  $(\Delta_{IBT}-\Delta_{WLC})/\sigma_{\Delta}$ ] (Becker, 1988; Morris, 2008). The actual computation accounts for the correlation observed across assessments for each outcome observed in our pilot data which is responsible for the different estimates of detectable ES's.

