### Summary of important changes after trial commencement (Trial 2):

- 1.) Given changes in treatment availability in Vermont between the pilot and present studies, the inclusion criterion that participants be waitlisted for agonist maintenance was modified to include participants not currently receiving opioid agonist treatment.
- 2.) Following an initial request (prior to trial commencement) by the funding agency to increase the originally-proposed 12-week duration to a similar 24-week duration in order to parallel that of Trial 1, the proposed sample size was then also reduced to align with that of parallel Trial 1.
- 3.) HIV, HCV, and opioid overdose knowledge post-tests were added to the Week 4 assessment.
- 4.) Compensation for intake and monthly assessments was increased from \$30 to \$75 to facilitate timely recruitment.
- 5.) Remote study sites were broadened to include locations that were convenient to participants (e.g., municipal office, fire station, community substance treatment facility).
- 6.) With the onset of the COVID-19 pandemic, the following modifications were made to the study protocol in situations where participants were at high-risk and/or currently experiencing COVID-19 symptoms: participants were permitted meet with study staff less frequently or remotely via phone or UVM's institutionally-supported Zoom platform to reduce the risk of COVID-19 transmission; biochemical samples may be omitted or collected using modified procedures to reduce risk of COVID transmission.

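### Trial 2's analyses were not revised when the target fell from 200 to about 50: the IBT-only site-by-time GEE will often be inestimable, and Breslow-Day and ordinary logistic regression fail if the pilot's 0% control rate recurs

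*Supplement*

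**What the plan says.** Trial 2, Statistical methods, makes 24-week abstinence the primary outcome and tests it with a "Cochran-Mantel-Haenszel (C-M-H) chi square test with site as the stratification variable". It adds three further analyses:

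- **Homogeneity:** "The Breslow-Day test will be used to test homogeneity of the treatment effects across sites".
- **Covariate adjustment:** logistic regression where baseline covariates are confounded with treatment. Trial 1 uses the same sentence: "If applicable, logistic regression will be used to adjust for baseline covariates confounded with treatment group".
- **Trend:** a GEE for abstinence over the monthly assessments, within the IBT group only. "Fixed factors will include recruitment site and the within-subject factor, assessment time, along with their interactions".

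The Trial 2 Study Design section plans 200 participants: 100 at UVM and 50 at each of two rural health centers, with equal arms.

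Trial 2's list of changes after commencement says the sample was reduced to match Trial 1. Trial 1's own list gives a target of 50. The Trial 2 list also says: "Remote study sites were broadened to include locations that were convenient to participants (e.g., municipal office, fire station, community substance treatment facility". Neither list mentions a change to the analysis. The documents give no definition of site for analysis, no pooling rule and no sparse-data fallback.

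The pilot found no waitlist (WLC) participant abstinent at Weeks 4, 8 or 12. IBT abstinence was 88%, 84% and 68%. Trial 2's Sample size justification plans for 60% versus 15%.

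**The concern.** Models that suit 100 IBT participants at three sites may not suit about 25. In the GEE, a site-by-visit cell in which everyone or no one is abstinent sends its log-odds to infinity, so the interaction cannot be estimated. If no WLC participant is abstinent, the treatment odds ratio is infinite. Ordinary logistic regression then does not converge (separation), and Breslow-Day has no finite common odds ratio to test against.

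The trend, homogeneity and adjusted analyses are at stake. If they fail, replacements would be chosen after the outcomes are known. The coding of site, which enters the primary test, would also be settled late.

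**Working it through.** **Inputs.** About 25 per arm is inferred from the two change lists and the equal arms originally planned. Splitting the IBT arm in the planned proportions (half at UVM, a quarter at each rural site) gives about 13/6/6. There are six visits. IBT rates at Weeks 4, 8 and 12 are the pilot's. Rates of 65%, 62% and 60% at Weeks 16, 20 and 24 are assumed, declining to the planned 60%. Alpha is .05, taken as two-sided.

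**1. The plan's own power figure.** The section says "power is estimated to be greater than 95% using" alpha .05 "if true abstinence rates are as low as 60% vs. 15% for IBT and WLC groups, respectively". The formula is Φ{[0.45√n − 1.96√(2 × 0.375 × 0.625)] / √(0.60 × 0.40 + 0.15 × 0.85)}.
- n = 100 per arm: (4.5 − 1.342)/0.606 = 5.21, so power exceeds 99.9%. The stated figure reproduces.
- n = 25 per arm: (2.25 − 1.342)/0.606 = 1.50, so power is 93.3%.

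**2. GEE.** Three sites × six visits = 18 parameters. A cell with n people and abstinence p is all-or-none with probability pⁿ + (1 − p)ⁿ:

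| Week | p | n = 6 | n = 13 |
|---|---|---|---|
| 4 | 0.88 | 0.464 | 0.190 |
| 8 | 0.84 | 0.351 | 0.104 |
| 12 | 0.68 | 0.100 | 0.007 |
| 16 | 0.65 | 0.077 | 0.004 |
| 20 | 0.62 | 0.060 | 0.002 |
| 24 | 0.60 | 0.051 | 0.001 |

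If visits were independent, the chance that no cell is all-or-none is 0.258 at each six-person site and 0.716 at UVM. Then 1 − 0.258² × 0.716 = 95%. Latent-normal simulation with within-person correlation up to 0.7 lowers this to 87%. Other settings, over the same correlations:
- Flat 60% at every visit, sites 13/6/6: 34–47%.
- Pilot-like rates, original IBT sizes 50/25/25: about 10%.
- Pilot-like rates, two sites (13/12): 46–52%. Recoding site alone therefore does not mend the model.
- Pilot-like rates, site and time main effects only: the most exposed margin is everyone abstinent at Week 4, 0.88²⁵ = 4%.

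**3. Breslow-Day and logistic regression.** The chance of no abstinent WLC participant is (1 − p)²⁵: 100% at p = 0, 60% at 2%, 28% at 5%, 7% at 10% and 1.7% at 15%. Simulation with two or three sites, counting Breslow-Day as undefined when the Mantel-Haenszel odds ratio is 0 or infinite or fewer than two strata are informative, gives 100% at 0%, about 27–31% at 5% and about 2% at 15%. Logistic separation on treatment occurs at almost the same rates. For scale, the exact 95% upper limit for the pilot's 0 of 25 is 1 − 0.025^(1/25) = 13.7%, just below the planned 15%.

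**4. Primary C-M-H test.** Simulated with 50 participants and IBT abstinence of 60%:
- Three planned sites: on average 0.02–0.3 participants fall in strata with zero weight. Power is about 93% at 15% WLC and above 99% at 0–5%.
- UVM versus remote: essentially nobody is lost, and power at 15% WLC is about 93–94%.
- 25 at UVM and the other 25 spread at random over 6, 10 or 15 locations, each its own stratum: about 45, 40 or 36 of 50 contribute. Power at 15% WLC is about 90%, 87% or 85%. At 0–5% WLC it is still at least 98%.

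**The case against.** A reader might infer that the primary test now drops participants and loses power. The documents do not support that. The Study Design section names three recruitment sites, and the GEE sentence refers to recruitment site. The change list widens where remote visits take place; it does not call those places analysis strata or give their number. With the planned sites almost nobody is lost. The power loss also appears at the planned 15% WLC rate, not at a rate near zero, so the two problems do not occur together.

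A reader might also count any site with no abstinent WLC participant as a Breslow-Day failure. It is not: the test remains computable while the common odds ratio is finite, although its large-sample approximation is poor with six or seven WLC participants at a rural site.

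Other points stand in part:
- The pilot lasted 12 weeks. Trial 2 lasts 24, with changed treatment availability and wider eligibility, so 0% may not recur. At 15%, failures are rare.
- The logistic model is conditional and does not name site.
- The GEE is a secondary analysis in one arm, so WLC abstinence has no bearing on it. With linear time it would need 6 parameters rather than 18. However, the plan calls time a within-subject factor, which most naturally means categorical.

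These limit the scope. They do not supply a definition of site, a fallback, or a GEE that 25 people can support.

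**Conclusion.** The concern holds for the secondary and supporting analyses, not for the validity of the primary test.

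- **GEE (main defect).** As written, with categorical time and three sites, it will usually not be estimable at pilot-like rates (87–95% of simulated trials) and often not at a flat 60% (34–47%). This needs neither extra locations nor a low WLC rate. It rests on about 25 IBT participants split 13/6/6 and on the assumed later-visit rates.
- **Breslow-Day, and logistic regression in both trials.** Failure is certain at the pilot's 0% WLC rate, occurs in about 27–31% of trials at 5%, and in about 2% at the planned 15%. A plan should cope with the result its own pilot produced.
- **C-M-H.** It is valid, with about 93% power for 60% versus 15%, at the planned sites. Power falls to about 85–90% only if each of 6 to 15 remote locations were coded as its own stratum. Those counts are assumptions, but the undefined term leaves that coding open.

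The sponsor should change this before analysis.

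**What to change.** Amend the Statistical methods as follows:

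1. Define site as UVM versus remote in every Trial 2 analysis, including the C-M-H test.
2. Remove the site-by-time interaction from the IBT GEE. Keep site and time main effects, or use linear time.
3. Use Firth-penalised logistic regression for any adjusted analysis in both trials.
4. When cells are sparse, replace Breslow-Day with risk differences by stratum or an exact homogeneity test.

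An exact mid-p C-M-H test is optional. The cost is analysis-plan wording, with no new data. The downside is that differences between individual remote locations are not modelled, which about 25 remote participants could not support in any case.

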To begin evaluating IBT generality and scalability, we will partner with federally qualified health centers (FQHCs) in two rural Vermont counties. FQHCs are non-profit health centers that are located throughout the US and have an overarching mission to provide primary care services specifically to medically underserved areas and populations. UVM will serve as the coordinating center and primary recruitment site where we will enroll 100 participants (50 IBT, 50 WLC). Two rural FQHCs will serve as recruitment sites for an additional 100 participants (50 IBT, 50 WLC), with half recruited at each clinic. The clinics are located in Orange and Addison counties, which are similar in terms of population density and median household income (42.1 vs. 48.0 inhabitants per square mile and \$52,079 vs. \$55,800, respectively). We will establish a mobile IBT team consisting of a nurse and research assistant (RA) who will travel to each clinic to conduct study visits. Considering that IBT involves essentially weekly visits (2 scheduled visits + 2 random call-backs per month), this will be easily accomplished. Our IBT components are also highly transportable (i.e., Med-O-Wheel, IVR monitoring, HIV+Hepatitis iPad application), which will further support the delivery of IBT at sites outside of our centralized university setting. Finally, it is worth noting that, for rural areas that continue to lack sufficient opioid treatment providers, this mobile IBT paradigm could represent an altogether new approach for BUP delivery to individuals living in underserved areas.

**Procedures:** Describe all procedures (sequentially) to which human participants will be subjected. Identify all procedures that are considered experimental and/or procedures performed exclusively for research purposes. Describe the types, frequency and duration of tests, study visits, interviews, questionnaires, etc. Include required screening procedures performed before enrollment and while on study. Please provide in table, list or outline format for ease of review. (describe and attach all instruments)

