**Vulnerable Populations:** Explain the rationale for involvement of special classes of subjects, if any. Discuss what procedures or practices will be used in the protocol to minimize their susceptibility to undue influences and unnecessary risk (physical, psychological, etc.).

☒ Not applicable

**Number of Subjects:** What is the anticipated number of subjects to be enrolled at UVM/UVM Medical Center and in the case of a multi-center study, with UVM/UVM Medical Center as the lead, the total number of subjects for the entire study.

The anticipated number of subjects to be enrolled in the study is 200 (100 per experimental condition).

**Inclusion/Exclusion Criteria:** Eligibility and ineligibility criteria should be specific. Describe how eligibility will be determined and by whom. Changes to the eligibility criteria at a later phase of the research have the potential to invalidate the research.

Participants must be  $\geq 18$  years old, in good health, meet DSM-5 criteria for opioid use disorder and provide an opioid-positive urine at study intake. Consistent with our prior BUP studies, those with a significant psychiatric or medical illness that may interfere with consent or participation will be excluded, as will those who are pregnant or nursing. Those dependent on sedative-hypnotics will be excluded, due to the medical risks and notably low success rates with sedative-dependent opioid abusers (Stitzer & Chutuape, 1999). Intake information will be reviewed by the PI ([name]) and study physician ([name]), who will determine and document whether the participant is eligible and healthy to participate.

**Inclusion of Minorities and Women:** Describe efforts to include minorities and women. If either minorities or women are excluded, include a justification for the exclusion.

The study will include minorities and women. We will do all that we can to assure that women and minorities are represented in the research, including using a wide range of recruitment sources to ensure that information regarding this project reaches as diverse of a population as possible (e.g., flyers posted in multiple local neighborhoods, advertisements in the widely-distributed primary local newspaper as well as alternative local papers).

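### Trial 2 stratifies its primary test by site, but its PROC MIXED comparisons of the arms name no site term; adding setting would modestly sharpen the treatment contrasts at each assessment.

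*Supplement*

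**What the plan says.** The Study Design section of the Trial 2 protocol plans 100 participants at the university site, 50 per arm. It then adds: "Two rural FQHCs will serve as recruitment sites for an additional 100 participants (50 IBT, 50 WLC), with half recruited at each clinic". The arms are therefore meant to be equal within each setting, for 200 in all.

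The Trial 2 Statistical methods section treats site as follows:

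- **Primary outcome (24-week abstinence):** a Cochran-Mantel-Haenszel "chi square test with site as the stratification variable", plus a Breslow-Day test of homogeneity across sites.
- **Abstinence at the other months:** Bonferroni-adjusted C-M-H tests.
- **Trend in abstinence within the IBT arm:** a GEE. The next sentence gives the fixed factors as recruitment site, assessment time and their interactions.
- **Continuous outcomes** (illicit opioid and IV use frequency, ASI, BDI, knowledge scores): "Repeated measures analyses of variance (SAS, PROC MIXED) will be used to compare groups on continuous outcomes". Partial F-tests of treatment at each assessment follow if treatment-by-time is significant. No site term is named.

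The Trial 2 summary of changes later records that "the proposed sample size was then also reduced to align with that of parallel Trial 1" and that "Remote study sites were broadened to include locations that were convenient to participants". Trial 1's target had become 50. The split by site is not restated for the smaller sample.

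**The concern.** Site is part of the design and of the primary test, yet it is absent from the one family of between-arm models that covers most secondary outcomes. When arms are balanced within a factor and the model ignores that factor, differences between its levels stay in the residual. The estimated standard error then exceeds the true one. When arms are not balanced within the factor, chance imbalance moves the estimate itself. Either way the contrasts at each assessment give up some precision, in a trial whose target was cut to about 25 per arm (reading the aligned target of 50 as the total). Leaving the term unstated also leaves a modelling choice open until data are in hand.

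**Working it through.** **Which model the fixed-factor sentence describes.** It directly follows the GEE sentence, which is restricted to the IBT arm. It lists site and time but not treatment, so it cannot be the full specification of a model that compares arms. The PROC MIXED sentence comes after it and lists no terms; treatment and time appear only through the interaction test. The rule on baseline covariates does not bring site in either. It requires a significant difference between arms, which site will not show if arms are equal within site.

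**The plan's own figures.** The primary power claim (above 95% for 60% vs 15%, 100 per arm, two-sided .05 assumed) reproduces at above 0.999. For BDI, Trial 1's ES of 0.42 at 50 per arm and 80% power implies an SD of change of 0.42 / (2.802 × √(2/50)) = 0.750 baseline SD, or a correlation of 1 − 0.750²/2 = 0.72. Carried to Trial 2 (ES 0.30, 100 per arm), 0.30 / (0.750 × √(2/100)) = 2.83, and power is Φ(2.83 − 1.96) = 0.81, against 80% stated. That calculation is for change from baseline, so a constant setting effect does not touch it.

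**Inputs for the contrast at one assessment.** Half of participants are in each setting (Study Design). The settings differ by d within-site SD. No document gives d, so 0.3, 0.5 and 0.8 are assumptions.

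**Formulas.** Two equal strata that differ by d add d²/4 to the residual variance when setting is omitted, so V = 1 + d²/4. The SE ratio is √V.

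- *Arms balanced within setting:* the estimate and its true variance do not change, but the test divides by an SE that is √V too large. Type I error is 2Φ(−1.96√V). A contrast with 80% power when setting is included has power Φ(2.802 − 1.96√V) without it.
- *Balance not enforced:* the true variance of the unadjusted estimate itself grows by V. Power without setting is Φ(2.802/√V − 1.96), ignoring the small cost of chance imbalance in the adjusted model.

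| d (assumed) | V | √V | Type I error, balanced | Power, balanced | Power, not enforced |
|---|---|---|---|---|---|
| 0.3 | 1.0225 | 1.011 | 0.047 | 79.4% | 79.1% |
| 0.5 | 1.0625 | 1.031 | 0.043 | 78.3% | 77.6% |
| 0.8 | 1.16 | 1.077 | 0.035 | 75.5% | 73.9% |

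With 25 per arm and no enforced balance, the SD of the arm difference at d = 0.8 is √(2/25) × 1.077 = 0.305 without setting, against about √(2/25) = 0.283 with it.

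**Simulation check** (20,000 runs; sites of 50/50, 25/25 and 25/25 per arm; site holding 10% of the variance at one assessment). The estimates with and without site are identical. The true SD of the difference is 0.136; the model SE is 0.141 without site and 0.134 with it. Type I error without site is 0.042. For a true difference of 0.396 SD, power is 0.804 without site and 0.833 with it. With site holding 20% of the variance, type I error without site is 0.029.

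**The case against.** The strongest reply is that the plan is silent rather than wrong. It never says that site is excluded from PROC MIXED, and a generous reader could extend the fixed-factor sentence to the sentence after it. It is right that the plan does not exclude site. But the fixed-factor sentence omits treatment and follows an IBT-only model, so as written the between-arm comparison has no site term.

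The second reply limits the reach, and it stands. A setting effect that is constant over time cancels from treatment-by-time, which gates the tests at each assessment, and from change from baseline, on which the secondary power statement rests. Only secondary outcomes are involved, and type I error is not inflated.

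The third reply is that d is unknown. This also stands; at d = 0.3 the effect is negligible.

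Two stronger readings are tempting. A reader might infer that omitting site biases the arm difference or makes it truly more variable even with balanced arms. It does not: only the model SE changes. A reader might also infer that 2%, 6% or 16% amounts to discarding about 1, 3 or 7 of 50 participants, from 50 × (d²/4)/V. Under balance that describes interval width only, since the estimate keeps its precision. It describes a real loss only if balance was not enforced. The documents give planned counts at 200, do not say that randomization was stratified by site, and do not restate the split after the reduction.

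**Conclusion.** The point holds as a modest improvement to the secondary analysis. As written, the PROC MIXED comparisons carry no site term although the design and the primary test do. With arms balanced within setting, the result is an unbiased estimate with a model variance 2%, 6% or 16% too large and conservative tests. Without enforced balance, the estimate's own variance grows by the same factors. On the assumed range, power of 80% falls to between about 79% and 74%. This rests on equal halves in the two settings, on d (which no document supplies), and on contrasts at a single assessment. The primary analysis is not affected, and neither, if the setting effect is constant over time, are the treatment-by-time and change-from-baseline contrasts.

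**What to change.** In the Trial 2 Statistical methods, state that every between-arm PROC MIXED model includes setting (university versus remote, all remote locations pooled) and setting-by-time as fixed effects, alongside treatment, time and treatment-by-time. Pooling is needed because the broadened remote locations would otherwise form very small cells. Define site once, in those same two levels, and use it for the C-M-H strata as well; otherwise the primary and secondary analyses would still disagree on what site means. State also whether randomization was stratified by setting, and what split applies to the reduced sample. The cost is a short addition to the text, one degree of freedom for setting and a few for setting-by-time. In the balanced case at 25 per arm, losing those degrees of freedom is almost free even if settings do not differ.
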